#### Secondary outcomes

The secondary outcome measures consist of PNC service use and pregnancy outcomes. Postnatal care service use is a maternal health care service use after birth within 45 days or 6 weeks. The participants will be considered as a user of PNC services if they have at least one PNC follow-up. Pregnancy outcome is the final result of fertilization events such as a live birth (full term or preterm), still birth, spontaneous abortion or induced abortion, low birth weight and normal birth weight. All the participants of this trial will be interviewed for the secondary outcome at phases II and III data collection time. To assess secondary outcome measures, a structured, interview-based questionnaire, which includes a status of PNC follow-up and pregnancy outcome, will be used.

For both primary and secondary outcome measures, participants’ medical record will be used for cross checking to avoid social desirability effects during the interview (Fig. 3).

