#### Screening and enrollment procedure

In this study, pregnancy, GA and ownership of mobile phone will be used as the main selection and enrollment criteria. Hence, in the selected kebeles, first, all the reproductive-age women with a history of amenorrhea for the last 28 days, who do not use any family planning, and who own a mobile phone will be screened for pregnancy through beta-human chorionic gonadotropin (HCG) urine test. Then, the mothers who are found to be positive for the HCG urine test will be given a unique identification number (ID No) and screened for GA through their last menstrual period (LMP) and/or portable ultrasound (U/S) scan result. Next, those women of less than 16 weeks of GA will be registered as illegible for the study. Finally, for each control and intervention group, 320 pregnant women who fulfill the enrollment criteria will be selected by a simple random-sampling method (computer-generated random table) [23]. They will be registered with their ID No and mobile phone number on a computer tablet.

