#### Independent variables

Mobile-phone-based voice message

Socio-demographic characteristics (covariate)

Maternal health status (covariate)

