### Operational definitions

*Mobile-health* **=** the use of a mobile phone to support health care at individual, community or systems level*Maternal health care service utilization* **=** the women’s health care service use from conception to delivery and during postnatal period till 45 days or 6 weeks*Antenatal care service use* **=** maternal health care service use during pregnancy*Institutional delivery* **=** giving birth in health facilities*Postnatal care service use* = maternal health service use after birth within 45 days*Pregnancy outcome* ***=*** the final result of a fertilization event such as live birth (full-term or preterm birth), stillbirth, spontaneous abortion and induced abortion*Adverse pregnancy outcome* = includes maternal adverse outcomes and/or neonatal adverse outcomes*Maternal adverse outcome* = maternal illness or maternal near miss and/or maternal death*Neonatal adverse outcome* = neonatal morbidity and/or neonatal mortality*Stillbirth* **=** any fetus born at 28 weeks of gestational age or more with no heart beat or respiratory effort*Low birth weight* **=** birth weight less than 2500 g after viability*Preterm* **=** any birth occurring between 28 and 37 weeks of gestation*Abortion* **=** the termination of pregnancy before 28 weeks of GA*Maternal near miss* **=** a woman who nearly died but survived a complication that occurred during pregnancy, childbirth or within 45 days of termination of pregnancy*Maternal mortality* **=** the death of women during pregnancy or within 45 days of termination of pregnancy irrespective of the duration from any cause related to, or aggravated by, the pregnancy or its management but not from accidental or incidental causes*Neonatal mortality* **=** the death of infants with in the first 28 days of life*Institutional delivery* = child-birth attended by skilled health professionals*Maternal under-nutrition* **=** mother will be considered as undernourished if she has anemia and/or wasting or/and underweight or low weight-gain during pregnancy*Anemia* **=** mother will be considered as anemic if the level of hemoglobin is less than 11 g/dl which will be measured through the Hemocue machine*Severe anemia* = mother will be considered to have severe anemia if the level of hemoglobin is less than 7 g/dl which will be measured through Hemocue machine*Wasting* = mother will be considered to have wasting if the MUAC measurement is less than 18.5 cm*Underweight* = mother will be considered as underweight if her Body Mass Index (BMI) is less than 18.5 kg/m^2^

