### Statistical method

For primary and secondary outcomes, Relative Risk with 95% confidence interval will be estimated. The association of dependent and independent variables will be checked by using the chi-square test. For count data, further analysis will be done by using multivariate count data logistic regressions or the Poisson Regression Model will be used to examine the effect of treatment on trial arms and Kaplan-Meier survival analysis will be used to compare maternal health care service use over time among treatment and control groups. Moreover, to adjust for both the clustering effect of the districts with their respective HCs and the participant-level intracluster correction, Generalized Estimating Equation (GEE) models will be used. All the analysis will be done by using STATA software.

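### Gestational age at entry is not among the named covariates, so a difference in enrolment timing between the two districts would appear as an effect on pregnancy loss

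*Protocol article*

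**What the plan says.** **Entry.** The protocol article (Screening and enrollment procedure) starts screening with "all the reproductive-age women with a history of amenorrhea for the last 28 days", then applies a urine HCG test and dating by last menstrual period and/or ultrasound. After dating, "those women of less than 16 weeks of GA will be registered". Entry can therefore fall anywhere from about 4 weeks to just under 16.

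**Outcome.** The Secondary outcomes section defines pregnancy outcome as the end result of the pregnancy. Besides live birth, the categories include "still birth, spontaneous abortion or induced abortion, low birth weight and normal birth weight". The Operational definitions describe abortion as "the termination of pregnancy before 28 weeks of GA".

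**Analysis.** The Statistical method section says: "For primary and secondary outcomes, Relative Risk with 95% confidence interval will be estimated". It names regression models, and GEE to account for clustering. Its one time-to-event method is confined to service use: "Kaplan-Meier survival analysis will be used to compare maternal health care service use over time among treatment and control groups".

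**Covariates.** The Independent variables section lists the voice message and two covariate classes, "Socio-demographic characteristics (covariate" and "Maternal health status (covariate". Gestational age at entry is not named.

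**Allocation.** Under Randomization and sampling procedure, two districts are allotted by lottery, one to each arm, with one purposively chosen health centre in each.

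**The concern.** Abortion can be counted only if it happens after enrolment and before 28 weeks. A woman enrolled at 5 weeks is observed through the early weeks of pregnancy. A woman enrolled at 15 weeks is in the trial only because she got through those weeks. This is left truncation: the proportion with an observed loss depends on entry week, even when every woman has the same underlying risk.

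In an individually randomised trial, entry week would be balanced on average. Here each arm is a single district, and simple random sampling within a district reproduces whatever entry distribution that district has. If one district finds its pregnancies earlier, that arm will show more losses without any effect of the messages. The Discussion section of the article expects the intervention to lower adverse pregnancy outcomes, so an artefact in either direction would bear on a claim the trial hopes to make.

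**Working it through.** **1. The plan's own figure.** The documents give no figure for pregnancy loss. The stated sample size supplies the number per arm and the design effect. For 47% versus 60%, two-sided 5%, 80% power:

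- Uncorrected: n = [1.960·√(2·0.535·0.465) + 0.842·√(0.47·0.53 + 0.60·0.40)]² / 0.13² ≈ 230.
- With continuity correction: 246.
- 246 × 1.3 = 319.8, rounded up to the stated 320.

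The figure reproduces. It does not bear on this point beyond supplying 320 per arm and the design effect of 1.3, which gives an effective 320 / 1.3 ≈ 246 per arm.

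**2. Assumed inputs (not in the documents).**

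- Weekly loss risk: 3% in weeks 4-5, 2.5% in weeks 6-7, 1.5% in weeks 8-9, 0.8% in weeks 10-11, 0.4% in weeks 12-15 and 0.1% in weeks 16-27. All are multiplied by 0.5, 1 or 1.5 to give a range.
- Entry week uniform over a window, with windows differing between arms by one or two weeks in the mean.
- No intervention effect.

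**3. Formula.** Observed risk for entry at week g = 1 − ∏(1 − h_w) over weeks g to 27. With the unscaled rates:

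- Entry at week 4: 1 − 0.97²·0.975²·0.985²·0.992²·0.996⁴·0.999¹² ≈ 17.0%.
- Entry at week 15: 1 − 0.996·0.999¹² ≈ 1.6%.

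The risk for an arm is the average over its entry window, and the spurious relative risk is the ratio of the two averages. The false-positive rate is that of a two-sided 5% z-test, Φ(z − 1.96) + Φ(−z − 1.96), with z = (p₁ − p₂) / √{[p₁(1−p₁) + p₂(1−p₂)]/n}.

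**4. Results.** Ranges run over the three scalings.

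| Entry windows (weeks) | Mean shift | Spurious RR | False-positive rate, n = 320 | With design effect 1.3, n ≈ 246 |
|---|---|---|---|---|
| 8-12 v 9-13 | 1 week | 1.25-1.26 | 7-11% | 7-10% |
| 4-15 v 6-15 | 1 week | 1.34-1.36 | 10-21% | 9-17% |
| 6-10 v 8-12 | 2 weeks | 1.62-1.65 | 20-48% | 17-39% |
| 4-15 v 8-15 | 2 weeks | 1.83-1.88 | 25-58% | 20-47% |

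One row in full (6-10 v 8-12, scaling 0.5): p₁ = 0.0392, p₂ = 0.0238, RR = 1.65. With n ≈ 246, SE = 0.0157 and z = 0.98, so the false-positive rate is about 0.165, against a nominal 0.05.

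**5. Dependence on the assumed curve.** A second set of assumptions puts every woman in an arm at the same entry week, with total loss of 5-20% from week 4 to week 28:

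| Weekly hazard | RR, week 8 v 10 | RR, week 8 v 12 |
|---|---|---|
| Constant | about 1.1 | 1.23-1.24 |
| Falling 18% per week | about 1.5 | 2.2-2.3 |
| Ten times higher before week 12 | about 1.5 | 3.3-3.5 |

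The direction is the same under each shape; the size is not. With equal entry timing in the two districts, RR = 1.0 throughout.

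**The case against.** **No passage shows that entry timing differs.** Both arms follow one screening procedure with the same HCG test, dating, gestational limit and sampling of 320. This stands. A reader might infer that the pregnancy-outcome comparison is biased as planned, but the documents support only that it is unprotected if timing differs.

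**A separate comparison of spontaneous abortion is an inference.** The article lists it as one category and does not say how categories will be split or combined. It also names regression and GEE beside the relative risk, so a purely crude analysis should not be taken as fixed. This stands, and the point is therefore put as one about an unadjusted comparison of pregnancy loss.

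**The covariate list is short and broad, and a condensed article may leave detail to a fuller plan.** This stands in part. Maternal health status could be stretched to include gestational age, but no section says so, and the Outcome measures section lists gestational age under eligibility, apart from maternal health conditions. The article does name its covariates, and adding one already determined costs nothing.

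**The magnitudes are assumed.** True. The largest come from a window in which one district enrols nobody before week 8 despite identical screening. Ignoring the plan's design effect would also overstate the false-positive rates (up to 21% and 58% rather than 17% and 47%).

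**The primary outcomes.** A reader might extend the point to antenatal care use and institutional delivery, since entry week affects how many messages a woman can receive. No calculation supports a bias there, and the truncation argument concerns pregnancy loss only.

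**A delayed-entry analysis needs the gestational week of each loss.** No section says that week is recorded. This stands, so such an analysis cannot be called free.

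**Conclusion.** The point holds in conditional form. The wide entry window, the relative-risk analysis of an outcome that includes spontaneous abortion, the single district per arm and the absence of entry gestational age from the named covariates are all in the article. Together they leave the pregnancy-loss comparison open to an artefact if the districts enrol at different gestational ages.

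Under the main set of assumed loss rates, with no true effect and a design effect of 1.3, a one-week difference in mean entry gives a relative risk of about 1.25 to 1.36 and a false-positive rate of about 7-17%. A two-week difference gives about 1.6 to 1.9 and about 17-47%. These figures show scale only: the loss rates and entry windows are assumptions, and flatter or steeper loss curves give smaller or larger ratios. The finding concerns one component of a secondary outcome. It does not show that a bias exists.

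**What to change.** 1. In the Independent variables section, add gestational age at enrolment as a named covariate for the pregnancy-outcome models.
2. Tabulate gestational age at enrolment by arm. The Outcome measures section mentions comparing baseline characteristics with the general population, so the comparison between arms should be stated.
3. Where the gestational week of loss is available, add a sensitivity analysis of spontaneous abortion on the gestational-age scale, with delayed entry at the enrolment week and induced abortion as a competing event.

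**Cost.** Items 1 and 2 are wording changes, because gestational age is already determined at screening. Item 3 depends on the week of loss being recorded at interview or found in the medical record, which may mean adding a question. The changes remove the entry-timing artefact only: with one district per arm, every other difference between the districts remains confounded with the intervention.

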### Analysis plan: analysis of primary and secondary outcome

In this study, data will be collected at three phases. Phase I data collection will be done during enrollment time; phase II data collection will be conducted after 4 months of enrollment or after the eighth voice message; and end-line data collection or close-out time data collection (phase III data collection time) will be made after the 24th voice message. All the data will be checked for completeness at the time of data collection, coded and entered into Epi-Info-7 by using double-data entry method and they will be transported to STATA software Version 11 for analysis. Data cleaning will be done by the running of simple frequency distributions for internal consistency.

The report of this findings will be made according to the Consolidated Standards of Reporting Trials (CONSORT) standards for reporting RCTs. This is a behavioral intervention which is unlikely to cause adverse effects. Hence, the analysis will be done after the close-out time of the data collection. Intention-to-treat (ITT) principles will be used for primary outcome analysis; therefore, all the participants will be analyzed according to the arms they will be randomized to. During ITT analysis, the participants lost to follow-up, resulting in missing to maternal health care service use at close-out time of data collection, will be considered as non-health care service users.

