#### Phase II

This stage of data collection will be conducted after the eighth voice message or the fourth month of enrollment and the data collection will focus on maternal health condition, nutritional status and status of the voice messages which will be delivered to the intervention group, status of maternal health care service use among both intervention and control groups. During this period, data related to maternal health conditions will be collected through the same tools which will be used in phase I. In addition, data related to maternal health care services using status and voice message will be collected through a structured, interview-based questionnaire with confirmation of voice messages from their mobile phone.

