#### Control arm B

Participants in the control group will receive existing SOC which informs them about the advantages of maternal health care service use at HCs, informing them about the service which is given free of charge and giving appointments for regular follow-up. Unlike the intervention group, however, these participants will not be sent the voice message to remind for appointment and information about the advantage of maternal service use. With regards to the data collections, a house-to-house survey will be made among the households which will be identified with pregnant mothers who fulfill the inclusion and enrollment criteria. The three phases of the survey (I, II and III) will be made to collect data from the mothers who are in the trial. The survey will focus on maternal socio-demographic status, maternal health conditions, nutritional status, and health care service use and pregnancy outcome. The data collection tools will be the same for both trial arms (Trial arms A and B), except for mobile-phone-based voice message status.

For either intervention or control group if the study participants move from the study area before the study is completed, or withdraw from the study before the final data collection period, they will be registered as dropouts to follow-up.

Assuming that all mothers may give birth at different GAs their status of delivery will be tracked by fieldworkers and health professionals at selected HCs (Fig. 2).

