#### Primary outcome measures

This study has two primary outcomes (proportion of ANC use and institutional delivery). The assessment of outcome measures will be conducted starting from phase II data collection time (after the eighth voice message or 4 months from the date of enrollment) and at phase III data collection time (after the 24th voice message or at close-out time off study). All the participants in the trials will be interviewed about their ANC visits and place of delivery by using a structured questionnaire. Antenatal care service use is defined as maternal health care service use during pregnancy. The participants will be considered as an ANC service user if they have at least one ANC visit. Institutional delivery is giving birth at a health facility (Fig. 3).

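### Coding every woman missing at close-out as a non-user can, read literally, recode documented ANC users, and it biases the risk ratio in either direction if loss differs by arm

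*Protocol article*

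**What the plan says.** The missing-data rule is in the protocol article under Analysis plan: analysis of primary and secondary outcome. In the intention-to-treat analysis of the primary outcomes, women who drop out, "resulting in missing to maternal health care service use at close-out time of data collection, will be considered as non-health care service users". No exception follows.

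Four other places bear on it:

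- Primary outcome measures sets a threshold that one visit meets: "The participants will be considered as an ANC service user if they have at least one ANC visit". It also says: "The assessment of outcome measures will be conducted starting from phase II data collection time".
- Phase II (about four months after enrolment) collects "status of maternal health care service use among both intervention and control groups".
- Control arm B applies one dropout definition to both arms. It covers women who "move from the study area before the study is completed, or withdraw from the study before the final data collection period", and so includes women already interviewed at Phase II. The same section says of deliveries that "their status of delivery will be tracked by fieldworkers and health professionals at selected HCs".
- Secondary outcomes says, for primary and secondary outcomes alike, that the "medical record will be used for cross checking to avoid social desirability effects during the interview". Records are given no other role.

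The only stated check on loss is under Sensitivity and per-protocol analysis. It is restricted to women who completed follow-up to the 24th voice message, and it leaves out those with no ANC visit and a birth outside a facility.

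**The concern.** Having had one ANC visit cannot later become untrue. A woman whose visit is recorded at Phase II and who then moves away is a user under the outcome definition, yet a non-user under the analysis rule as worded. Institutional delivery is different. It is usually still unknown at Phase II, so for that outcome the rule mostly imputes failure rather than replacing an observation, although a facility birth tracked before the woman was lost could also be recoded.

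Scoring missing as failure is often thought cautious. In a comparison of two arms it is not: it lowers the arm that loses more women, whichever that is. Unequal loss could therefore create an apparent effect or hide a real one, in the analysis on which the trial's conclusion rests.

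**Working it through.** **Inputs from the protocol.** 47% (control) and 60% (intervention) for institutional delivery, from Sample size determination. Two-sided 5% level, 80% power, design effect 1.3 and 320 per arm, from the sample size assumptions. Background ANC use of 34%, from the Background. The effect measure is the relative risk (Statistical method). **Assumptions.** All loss rates, and any level of use other than these; the protocol gives no loss rate.

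**The plan's own figure.** For 47% v 60%, the two-sided formula gives 230 per arm, or 246 with continuity correction. 246 × 1.3 = 319.8, rounded up to 320. The figure reproduces and contains no allowance for loss.

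**Can ANC use already be on record before loss?** Enrolment is below 16 weeks' gestation after at least 28 days of amenorrhoea, so Phase II, 16 weeks later, falls at roughly 20 to 32 weeks. The protocol's window for the first visit closes at 24 weeks, so a woman enrolled at 8 weeks or later has reached its end by Phase II. If 34% to 80% of lost women had a recorded visit (assumed), the number recoded per arm is:

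- 10% loss: 320 × 0.10 × 0.34 = 10.9 to 320 × 0.10 × 0.80 = 25.6, so about 11 to 26 women.
- 20% loss: about 22 to 51 women.

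**Effect on the risk ratio.** Let true use be p in both arms, and let losses L_T (intervention) and L_C (control) be unrelated to use. Coded use is p(1 − L) in each arm, so the risk ratio under no effect is (1 − L_T)/(1 − L_C), whatever p is. For 5% v 15% this is 0.95/0.85 = 1.118. The rejection rate is that of a pooled two-proportion z-test at n = 320, and at an effective n of 320/1.3 = 246.

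No true effect, loss 5% (intervention) v 15% (control):

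| True use, both arms | Coded use | Difference | Rejection, n = 320 | Rejection, n = 246 |
|---|---|---|---|---|
| 34% | 32.3% v 28.9% | 3.4 points | 15% | 13% |
| 47% | 44.7% v 40.0% | 4.7 points | 23% | 18% |
| 60% | 57.0% v 51.0% | 6.0 points | 33% | 27% |
| 80% | 76.0% v 68.0% | 8.0 points | 62% | 51% |

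The 47% row uses the planning rate for delivery. ANC use of at least one visit may lie elsewhere, hence the range.

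Other losses, no true effect, 47% use:

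- 5% v 10%: risk ratio 0.95/0.90 = 1.056; rejection 9% (8% at n = 246).
- 20% v 5%: risk ratio 0.80/0.95 = 0.842, now against the intervention; rejection 44% at n = 320.
- Equal 10%: risk ratio 1.00; rejection 5%.

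**Under the planned effect (60% v 47%).**

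- Equal 10% loss: 0.540/0.423 = 1.277, the same as 0.60/0.47. The risk difference falls from 13 to 11.7 points, and power from 83% to 74% (effective n 246, no continuity correction).
- Loss of 15% v 5%: 0.510/0.4465 = 1.142, power 29%.
- Loss of 5% v 15%: 0.570/0.3995 = 1.427.

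**What keeping recorded ANC use achieves.** Take 80% true use, loss 5% v 15%, and let q be the share of eventual users already recorded at Phase II. Coded use becomes p(1 − L) + pLq.

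- q = 50%: 78.0% v 74.0%, risk ratio 1.054, rejection 22% (18% at n = 246).
- q = 80%: 79.2% v 77.6%, risk ratio 1.021, rejection 8% (7%).
- q = 100%: no bias.

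Keeping recorded visits shrinks the bias, but what is still unknown needs its own treatment.

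**The case against.** **A milder reading exists.** The rule applies to women whose service use is missing, and a woman with a visit recorded at Phase II might be held not to be missing for ANC. A reader might infer that the protocol orders recorded visits to be discarded; it does not say so. But the sentence ties missingness to close-out and makes no exception. If the milder reading is meant, the wording has to say it.

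**Unequal loss is not shown.** A reader might infer that the control arm will lose more women because only the intervention arm is messaged every two weeks, or because the urban shares differ (18.46% v 9.01%). The documents do not establish this. They describe the districts as similar, survey both arms at the same three phases, track deliveries without distinguishing the arms, and register phone numbers in both. Unequal loss is plausible, but its size and direction are open.

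**Equal loss does not dilute the planned effect measure.** This stands: the risk ratio is unchanged, and only the risk difference and power suffer.

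**A completers analysis is planned.** If loss is unrelated to use, a sound one would give 47% v 47% and expose a false effect. This one is not sound. It is defined by a 24th message that controls never receive, it excludes women partly on their outcome, and it drops lost women instead of using their recorded visits.

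**Detail can be left to an analysis plan.** This holds for the choice of imputation model. It does not cover a rule that the article itself fixes for the primary analysis.

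**Conclusion.** The concern stands in limited form. As worded, the primary rule can turn documented ANC users who later leave into non-users, in conflict with the protocol's own outcome definition. For institutional delivery it is mainly failure imputation. For both outcomes, loss unrelated to use but unequal by arm multiplies the risk ratio by (1 − L_T)/(1 − L_C): 1.12 for 5% v 15%, 0.84 for 20% v 5%. In the first case the false-positive rate is about 23% at 47% use and 62% at 80% use, or 18% and 51% with the stated design effect taken at face value.

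These are scenarios, not predictions. They rest on assumed loss rates and on loss being unrelated to use. A reader might infer that the trial is bound to produce a false benefit; the documents support only that the rule leaves the result open to bias in either direction, with no adequate check stated.

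**What to change.** Under Analysis plan: analysis of primary and secondary outcome:

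1. Count ANC use, and place of birth, documented at any phase before loss as observed, subject to the planned cross-check against medical records. An interview answer that the record contradicts must stay correctable, so a recorded outcome should not be made irreversible. Apply a missing-data rule only to outcomes still unknown.
2. For those, do not rely on missing = non-user alone. Report it beside an analysis that does not assume failure (for example imputation by arm from baseline and Phase II data) and one that varies the rate of use among missing women separately by arm.
3. Use delivery tracking in the same way in both arms. State that records at the selected health centres capture mainly local facility births, so they will not settle place of birth for women who moved away.
4. Under Sensitivity and per-protocol analysis, define completers by Phase III completion in both arms rather than by the 24th message, and do not exclude women on their outcome.

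The cost is wording and modest programming. The data sources are already planned.
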